In resource-limited clinical settings, identification of pathogens causing neonatal sepsis and analysing AMR profiles remain challenging. Isolated bacteria are increasingly resistant to first and second-line antibiotics recommended by the WHO [12,13]. Extended-spectrum beta-lactamases (ESBL)-positive *Klebsiella* and *E. coli* spp. are reported to become the most common causes of neonatal sepsis in SSA with rapid emergence of carbapenem-resistant *Enterobacterales* [14]. New and affordable antibiotics for the treatment of multi-drug resistant (MDR) neonatal sepsis are lacking [15], therefore, in addition to the development of new drugs, infection prevention control (IPC) is pivotal.

Establishing reliable sepsis and AMR diagnostics through blood cultures of neonates admitted to NCUs is crucial for identifying bloodstream infections and determining antimicrobial susceptibility, allowing clinicians to prescribe antibiotics more efficiently and appropriately. A large multi-country study, including our study site, published by NEST360 in 2023, highlighted a significant gap: while 70% of neonates were prescribed antibiotics, only 6% had blood cultures taken, missing critical opportunities for infection detection [16]. The authors concluded that there is an urgent need to improve diagnostics, and develop individualized strategies for the prevention and treatment of LOS in LMICs.

The peak incidence of LOS occurs between the second and third week of life [17] after being exposed to various factors in the NCU environment and exposures to various invasive procedures and antibiotics altering the neonatal microbiome [18]. The hypothesis of gut dysbiosis preceding the development of LOS and NEC in preterm babies has been developed, based on findings of alterations in their gut microbiome in terms of specific metabolites and reduced biodiversity before disease onset [19–21]. Importantly, several conventional culture studies have demonstrated concordance between isolates cultured in blood and bacteria residing in the infants’ gut [22,23].

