## Materials and methods

### Study design

This study will be a case-control study nested into a hospital-based, single-center, observational neonatal cohort. Recruited preterm neonates will be followed over their first 28 days of life. The primary clinical endpoint in this study is a blood culture (BC)-proven LOS. Secondary endpoints are clinical sepsis, NEC, death to clinical and/or BC-proven sepsis or NEC, death to any cause, or discharge from the hospital with or without sequelae.

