### Study population and sample size

The study participants will include inborn and outborn preterm neonates born at 28 + 0 to <34 weeks of GA admitted to the neonatal wards, and their respective mothers who consented to participate after a detailed description of the study has been given by trained study team members. Recruited preterm neonates should have a minimal weight of at least 1000 g and be enrolled within their first week of life. We will exclude infants whose mothers are below 18 years of age, have severe, life-threatening illness at the time of admission, and/or have severe comorbidities or severe congenital malformations. Furthermore, neonates or mothers who ever received probiotic supplements during pregnancy will be excluded from this study.

Sample size calculations considered all study objectives and the one requiring the largest sample size will be the basis to determine recruitment numbers. All eligible preterm neonates admitted to the neonatal unit during the 18-month study period will be recruited and closely followed up for 28 days each.

To answer the primary research question on the hypothesis of preterm neonates developing gut dysbiosis before the onset of sepsis we need to identify preterms with BC-proven sepsis, assess their microbiomes, and compare it with controls (matched for GA, sex, mode of delivery, type of feeding, and previous antibiotic exposure). Assuming a rate of BC-proven sepsis of 10% and 25% missed samples we expect to identify 72–135 bloodstream pathogens (positive BCs) with 54–101 complete sets of stool samples for microbiome analysis within 18 months [7,10]. According to Graspeuntner *et al.,* we then expect gut dysbiosis in 30% of the neonates without and 60% of the children with LOS [19].

Our minimal sample size considerations are based on the proportions of gut dysbiosis in children with and without LOS. Assuming an alpha level of 5% and a power of 80% a minimal study number of 84 children (42 with and 42 without LOS) is needed to reject the null hypothesis that no difference in the proportion of dysbiosis between both cases and controls. Cases are defined as preterm neonates who develop LOS and controls as preterm neonates who do not develop any clinical or culture proven sepsis during the observation period (after 72 hours of life).

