### Variables to predict LOS and gut dysbiosis

Variables have been selected based on a literature search and local clinical experience. Table 1 shows factors predicting LOS and gut dysbiosis that will be captured during the study period. Independent variables will be categorized as socio-economic, neonatal, maternal, and septic risk factors (Table 1).

**Table 1 pone.0325099.t001:** Candidate variables for predicting LOS and gut dysbiosis.

Socio-economic factors	Neonatal factors	Maternal factors	Septic risk factors
Maternal education level	Gestational age	Age at delivery	Invasive ventilation
Self-rated household income	Sex	Parity	Central line at least 48 hrs
Family health insurance	Birth weight	Previous stillbirths	Parenteral nutrition
	Multiple births	HIV status	Presence of any maternal risk factors
	APGAR score at 1 minute	Medical conditions	Type of feeding
	APGAR score at 5 minutes	Pregnancy complications	
	Place of birth	Maternal antibiotic exposure 3 months before delivery	
	Delivery complications		
	Antibiotic exposure and type		
	Type of delivery		

During the observational period of 28 days clinical signs and symptoms of LOS and/or NEC, BC results with phenotypic identification, and antibiotic susceptibility testing, the previous use and type of antibiotics, and the clinical outcomes, will be recorded by the study team in electronic data capture forms. Stool samples for microbiome analysis will be collected in a standardized manner on day 1–3, and days 7, 14, 21 (each ±3) and neonates’ type of feeding in the last 24 hours will be categorized as exclusive human milk (no formula given), breastfed mainly (>80% feeds breastmilk/human milk), formula feed (>50% of feeds include formula), only formula (no human milk), or no enteral feeding at all.

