### Statistical analysis

Descriptive statistics will be used to summarize the demographic and clinical characteristics of the study population, including gestational age, birth weight, gender, mode of delivery, and presence of comorbidities. Mean and standard deviation or median and interquartile range for continuous variables will be used and for categorical data frequencies or proportions will be described.

To answer the first objective on the incidence and risk factors of LOS, the incidence density will be calculated as the number of new cases of LOS divided by the total person-time at risk in the cohort. The person-time at risk will be calculated by summing the individual follow-up durations until the occurrence of BC-proven LOS (clinical sepsis, NEC, and death).

Cox-proportional hazard regression will be utilized to investigate the relationship between the risk factors and risk to develop primary and secondary endpoints. First, we will perform univariate cox-regressions for potential risk factors to identify individual risk factors, all variables considered relevant for the study question will be included in the multivariate cox-regression to adjusting for potential confounders. The hazard ratios (HRs) with the 95% confidence intervals (CIs) will be estimated for each risk factor. Etiological agents of LOS/NEC and the respective AMR patterns will be described as the proportion of isolates resistant to each antibiotic and according to international standard.

Microbiome analysis will be performed to evaluate gut dysbiosis in preterm infants prior to the development of LOS and in relation to the microbiome of the mother. Association of relative abundances of microbial species with the factors of gestational age, days of life, diet, and LOS will be limited to species that were found with a non-zero relative abundance in at least 40 stool metagenomes. Square root-transformed relative abundancies will be used and analysed using linear mixed effect (LME) models, where repeatedly collected microbiome data from each child is considered to cluster.

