Antibiotic interventions following a LOS diagnosis are likely to have a strong impact on the microbiome composition. Statistical analyses will be performed using the latest version of R statistical software. Cox regression will be calculated using the *survival* package and LME using the *lme4* package. In all above-mentioned association tests, samples taken after LOS diagnoses will be excluded from the statistical analysis since the present study focusses on the microbial pattern that precedes LOS.

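### Controls have no index age, so only the case stool series is cut at sepsis onset and a control's earlier antibiotic exposure has no reference date

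*Protocol article*

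**What the plan says.** All the statements are in the Protocol article.

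- **Controls** (Study population and sample size): "controls as preterm neonates who do not develop any clinical or culture proven sepsis during the observation period (after 72 hours of life"). The observation period comes from Study design: "Recruited preterm neonates will be followed over their first 28 days of life".
- **Matching** (same section): "matched for GA, sex, mode of delivery, type of feeding, and previous antibiotic exposure". Postnatal age and an index date are not in the list.
- **Stool schedule** (Variables to predict LOS and gut dysbiosis): "collected in a standardized manner on day 1–3, and days 7, 14, 21 (each ±3"), so the last scheduled stool can fall as late as day 24. Feeding over the preceding 24 hours is recorded alongside.
- **Cut-off** (Statistical analysis): "samples taken after LOS diagnoses will be excluded from the statistical analysis". No counterpart is given for controls.
- **Model** (Statistical analysis): "Association of relative abundances of microbial species with the factors of gestational age, days of life, diet, and LOS" is to be examined in linear mixed models, with stools clustered by child.
- **Sample size** (Study population and sample size): 42 cases and 42 controls, from dysbiosis in 60% and 30%, alpha 5% and power 80%.

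**The concern.** The primary question is whether dysbiosis comes before LOS, so a case and its control should be compared at the same age. A control has no LOS diagnosis, so the cut-off rule never touches its series. As written, the case is seen up to its onset and the control up to about day 21.

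The preterm gut flora changes over these weeks, and the plan itself names days of life as a factor. A difference in stool age or in number of stools can therefore appear as a difference in dysbiosis, or hide one.

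The matching has a related gap. Whether antibiotics came earlier is clear for a case, because they came before its onset. A control has no date to count back from, so treatment on day 20 could be counted as a match for a case with onset on day 10. The plan notes that antibiotics given after an LOS diagnosis are likely to change the microbiome strongly.

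**Working it through.** **1. The plan's own figure.** Two-sided 5%, 80% power, 30% against 60%, pooled variance, mean proportion 0.45:

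n = [1.96·√(2·0.45·0.55) + 0.8416·√(0.3·0.7 + 0.6·0.4)]² / 0.30² = 41.97, so 42 per group. The total of 84 reproduces. The expected case numbers do too: 720 × 10% = 72 and 1350 × 10% = 135; times 0.75 this gives 54 and 101.

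**2. Stool ages by day of onset.** Nominal days are 2, 7, 14 and 21 (day 2 stands for the day 1–3 window).

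| Onset | Case stools before onset | Mean case age | Control with all four stools |
|---|---|---|---|
| Day 5 | 2 | 2.0 | 11.0 |
| Day 8–14 | 2, 7 | (2+7)/2 = 4.5 | (2+7+14+21)/4 = 11.0 |
| Day 15–21 | 2, 7, 14 | 23/3 = 7.7 | 11.0 |
| Day 25 | 2, 7, 14, 21 | 11.0 | 11.0 |

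**3. Averages over assumed onset distributions.** The documents give no distribution, only that "The peak incidence of LOS occurs between the second and third week of life".

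| Onset (assumed) | Stools per case | Mean age, per child | Mean age, pooled | All four available |
|---|---|---|---|---|
| Normal, mean 14, SD 6, within days 4–28 | 2.6 | 6.3 | 7.1 | 12% |
| Uniform, days 7–21 | 2.5 | 6.1 | 6.4 | 0% |
| Uniform, days 4–28 | 2.7 | 7.0 | 8.1 | 29% |

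A control with a full series has 4 stools and mean age 11.0 in every row.

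**4. What this could do to the comparison of proportions.** The article does not say how several stools become one dysbiosis status per child, so two readings are tried.

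*(a) Last available stool, no true LOS effect.* Suppose the probability of dysbiosis falls from 50% on day 2 to 30% on day 21, linear on the logit scale. It is then 44.4% on day 7 and 36.9% on day 14. With onset uniform on days 7–21, half the cases end at the day-7 stool and half at the day-14 stool: (44.4 + 36.9)/2 = 40.7%, against 30% in controls. At 42 per group, with pooled standard error 0.104 and unpooled 0.104, the chance of rejection is Φ[(0.107 − 1.96·0.104)/0.104] ≈ 17.5%.

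| Age trend, day 2 to day 21 (assumed) | Cases appear | False rejection, 42 per group | 101 per group |
|---|---|---|---|
| 40% to 30% | 34–35% | 7–8% | 10–13% |
| 50% to 30% | 39–41% | 13–18% | 26–36% |
| 60% to 30% | 43–46% | 24–33% | 49–66% |
| 20% to 30% | 24–25% | 8–9% | 11–15% |

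The ranges span the two uniform onset distributions. In the last row cases look less dysbiotic than controls, so the direction reverses.

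*(b) Any dysbiotic stool, true difference 60% against 30% over four independent stools.* The per-stool probability in cases is 1 − 0.4^(1/4) = 20.5%. With 2.5 to 2.7 stools on average, the observed case proportion falls to 43–45%, and power at 42 per group falls from 80% to 24–30%.

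**5. After alignment.** For a case with onset on day 10, both infants contribute days 2 and 7, mean 4.5. The scheduled gap is zero by construction.

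**The case against.** The strongest counter-argument is the mixed model. It includes days of life and diet, so unequal stool ages need not bias the LOS coefficient for species abundances, and later control stools help to estimate the age trend. That stands. A reader might infer that the whole microbiome analysis is confounded by age, and the documents do not support this. Residual bias there would need a wrongly specified age trend, and the article does not say that age enters linearly. The coding may properly be left to the full analysis plan.

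Feeding is not undefined: it is recorded with each stool. What is missing is which record serves for matching. The match on day-20 antibiotics is something the text permits, not something it prescribes.

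A reader might also infer that never-septic controls are too healthy, so that the odds ratio is exaggerated and the control definition must be replaced. The documents do not carry this either. Sampling non-cases at the end of a fixed window is a recognised design. Excluding clinical sepsis has a rationale, because culture yield depends on diagnostic quality and some culture-negative infants may be missed cases. The article gives no clinical-sepsis rate, so no shift in the odds ratio can be computed from it. The definition also does not exclude necrotising enterocolitis or early-onset sepsis.

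Nor does the text set out to use briefly observed infants: follow-up is 28 days, with clinic visits and a day-28 call after discharge. Early discharge may, however, shorten some control stool series and narrow the gap shown above.

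None of this supplies an age alignment for the dysbiosis proportion or a reference date for a control's antibiotics.

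**Conclusion.** The point holds as a gap in alignment. The cut-off acts on cases only, and matching includes neither postnatal age nor an index date. A case with onset on day 10 has mean stool age 4.5 days against up to 11.0 in its control; across the assumed onset distributions the case mean is roughly 6 to 8 days. The days-of-life term reduces the consequence for species abundances. It does not reach the dysbiosis-proportion comparison that sets the sample size, the number of stools per child, or the antibiotic matching.

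Direction and size are not fixed by the documents. Depending on the age trend and on how stools are combined, the comparison could reject too often (7–33% at 42 per group in the scenarios tried) or lose power (to 24–30%). These figures rest on assumed onset distributions, assumed age trends, nominal stool days, full control series and unmatched tests. They show that the gap can matter, not how much it will.

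**What to change.** In Study population and sample size, and in Statistical analysis:

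1. Assign each matched control the case's age at LOS onset as its index age.
2. Require the control to be alive, under observation and sepsis-free at that age.
3. Define earlier antibiotic exposure and feeding type as of that age, for case and control alike.
4. For the case-control contrast, use only stools collected before that age in both.

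The never-septic definition can stay. Risk-set sampling that also admits infants who become septic later can be a sensitivity analysis; the two can equally be swapped, with never-septic controls as the sensitivity analysis. Either order is defensible if fixed in advance.

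The cost is revised wording and a re-programmed control draw, with no new samples. Later control stools drop out of the case-control contrast, though they can still inform the age trend in the mixed model.

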### Definitions of LOS, culture proven sepsis, clinical sepsis and NEC

LOS is defined as a bloodstream infection occurs after 72 hours of life, typically caused by nosocomial or community-acquired pathogens [26]. Culture-proven sepsis is identified when a bacterial or fungal pathogen is isolated from a sterile site, such as blood or cerebrospinal fluid. In contrast, clinical sepsis is diagnosed based on clinical signs and symptoms consistent with sepsis in the absence of a BC [27]. The signs and symptoms of neonatal sepsis range from nonspecific manifestations to hemodynamic collapse, requiring a high index of suspicion for timely diagnosis. This study will uniformly apply the WHO criteria for neonatal sepsis, which offer a standardized approach for identifying sepsis in preterm neonates [28]. LOS will be defined by the following criteria by responsible physicians, at least the presence of two signs as per WHO which includes difficulty feeding, convulsions, lethargy, tachypnoea, severe chest indrawing, hypothermia, hyperthermia, bulging anterior fontanelle and skin or umbilical infection with pus requiring systemic antibiotics for at least five days [28].

Cases will be categorized as culture-proven sepsis and clinical sepsis. Instances of positive BCs without accompanying signs or symptoms will be considered contaminants. Specifically, coagulase-negative staphylococci (CoNS) will be classified as a pathogen only if overt signs and symptoms consistent with sepsis, as defined by WHO criteria, are present; otherwise, CoNS will be regarded as contaminants [29]. To improve diagnostic accuracy where available, C-reactive protein (CRP) levels will be used as a biomarker during suspected sepsis episodes, with elevated levels supporting the presence of an inflammatory response [30].

In this study, NEC is defined and suspected clinically based on the presence of one or more of the most characteristic clinical features including abdominal distension, feeding intolerance, bilious vomiting or gastric aspirate and bloody stools, and if available, complemented by the finding on abdominal imaging of intramural gas, pneumoperitoneum or sentinel bowel loops [31,32].

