### Samples collection

#### Blood cultures.

To describe the etiological agents and AMR patterns of neonatal bloodstream infections, we will be collecting 1–2 ml sterile blood for cultures [35] in BD BACTEC™ Peds Plus BC bottles according to international recommendation guidelines in all participants developing signs and symptoms of LOS or NEC [36], without delaying antimicrobial treatment. For participants at risk of developing early onset sepsis (EOS), termed as presumed EOS according to standard treatment guidelines, and started on antibiotics based on risk factors, BCs will also be taken free of charge before initiation of treatment whenever possible. Another BC will be taken in cases of switching, adding, or escalating antibiotic therapy. An episode of sepsis will be classified as culture-proven sepsis or clinical sepsis depending on BC results and additional clinical information by the study physicians. The blood culture samples will be processed in the microbiology laboratory at MNH which is certified in accordance with the international standard (ISO 15189:2022).

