#### C-reactive Protein.

During a sepsis episode, C-reactive protein (CRP) will be taken as part of the laboratory workup using the Architect c8200 clinical chemistry analyzer. CRP result >10mg/l will be considered high and indicative of infection/inflammation.

When suspecting early-onset sepsis, CRP is routinely taken 48 hours after birth as part of the SOP of the NCU, as one of the parameters used to guide antibiotic treatment. If the CRP is high, antibiotics will be continued or changed depending on the clinical condition of the neonate while awaiting the BC results. If it is low, and the patient is clinically well and BC is negative, antibiotics are stopped and sepsis is ruled out.

For LOS, CRP is usually taken during or close to the sepsis episode and is interpreted as one of the diagnostic markers. The CRP taken during or closest (within 48 hours) to the sepsis episode will be recorded.

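### The rule that makes CoNS a pathogen when signs are present overlaps heavily with the trigger for taking the culture, so it filters few contaminants out of the primary endpoint

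*Protocol article*

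**What the plan says.** **Endpoint.** Under Study design: "The primary clinical endpoint in this study is a blood culture (BC)-proven LOS". The sample size section takes infants with proven LOS as the cases whose microbiomes are compared with matched controls. Controls have neither clinical nor culture-proven sepsis after 72 hours.

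**Contaminant rule.** The definitions section first sets a rule for any organism: "Instances of positive BCs without accompanying signs or symptoms will be considered contaminants". It then states that CoNS "will be classified as a pathogen only if overt signs and symptoms consistent with sepsis, as defined by WHO criteria, are present", and otherwise are contaminants. The sign standard for LOS is "at least the presence of two signs as per WHO which includes difficulty feeding, convulsions, lethargy, tachypnoea" and further signs. The list ends with a clause on systemic antibiotics for at least five days.

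**Culture trigger.** The Blood cultures section has cultures taken "in all participants developing signs and symptoms of LOS or NEC". Two further occasions are named. For presumed early-onset sepsis treated on risk factors, "BCs will also be taken free of charge before initiation of treatment whenever possible". Also, "Another BC will be taken in cases of switching, adding, or escalating antibiotic therapy".

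**CRP.** The definitions section uses CRP where available, as support. The C-reactive Protein section sets above 10 mg/l as high, treats CRP as one of the diagnostic markers for LOS, and adds: "The CRP taken during or closest (within 48 hours) to the sepsis episode will be recorded". Neither section makes CRP a condition for accepting CoNS. Episodes are classified by study physicians from the culture result and other clinical information.

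**The concern.** A rule that separates pathogen from contaminant is useful only if it brings in information beyond what led to the culture. Here the trigger is the appearance of signs and the acceptance criterion is the presence of signs. An infant whose signs have another cause, and whose bottle picks up CoNS during sampling, will usually satisfy both.

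Three results would be affected:

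- The incidence of proven LOS would be too high.
- CoNS and their resistance patterns would be over-represented in the pathogen and AMR description.
- The case group in the microbiome comparison would include infants without bloodstream infection, which weakens the contrast.

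Larger numbers can restore power, but they do not remove the first two distortions.

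**Working it through.** **Step 1. Trigger against criterion (after 72 hours)**

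| Reason for the culture | Are WHO-type signs present? | Can the rule reject a CoNS contaminant? |
|---|---|---|
| Two or more WHO signs | Yes, by definition | No |
| A single WHO sign | Below the two-sign standard | Yes |
| NEC features only | Mostly not on the WHO list | Yes |
| Antibiotic switch, addition or escalation | Not required by the text | Yes, if signs are absent |

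Cultures for presumed early-onset sepsis fall before the LOS window. The rule thus keeps some filtering, but none in the first row, which is the typical suspected-LOS culture.

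**Step 2. The plan's own figure**

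Inputs from the sample size section: dysbiosis 30% without and 60% with LOS, alpha 5% two-sided, power 80%. With pooled variance under the null, the mean proportion is 0.45 and

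n = [1.960·√(2·0.45·0.55) + 0.842·√(0.3·0.7 + 0.6·0.4)]² / 0.30² = 41.97, so 42 per group and 84 in total. This matches the stated figure.

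Expected cases: 720 × 0.10 = 72 and 1350 × 0.10 = 135. With 25% missed samples, 72 × 0.75 = 54 and 135 × 0.75 = 101 complete stool sets.

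**Step 3. Sensitivity to contamination**

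The article gives no contamination rate. Let c be the share of counted cases that are contaminants, and let these have the control dysbiosis rate of 30% (worst case). Then:

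- case proportion p = 0.60·(1 − c) + 0.30·c = 0.60 − 0.30c
- excess of counted over true incidence = c/(1 − c), with person-time taken as about unchanged
- power = Φ{[(p − 0.30)·√n − 1.960·√(2·m·(1 − m))] / √(0.21 + p(1 − p))}, where m = (p + 0.30)/2

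| c | p | Incidence excess | Power, 42 per group | Power, 54 per group | Power, 101 per group | n per group for 80% |
|---|---|---|---|---|---|---|
| 0 | 0.60 | 0% | 80% | 89% | 99% | 42 |
| 10% | 0.57 | 11% | 71% | 82% | 98% | 52 |
| 20% | 0.54 | 25% | 61% | 72% | 94% | 66 |
| 30% | 0.51 | 43% | 50% | 61% | 87% | 85 |

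**Step 4. Is 10–30% conceivable?**

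Suppose 20–50% of infants are cultured for signs, 1–10% of those grow CoNS by contamination and are all accepted, and true proven LOS is 10%. The first two ranges are assumptions. False cases are then 0.20 × 0.01 = 0.2% to 0.50 × 0.10 = 5% of infants, and their share of counted cases is 0.002/0.102 = 2% to 0.05/0.15 = 33%. The range of 10–30% is therefore possible, but the lower end of the assumptions gives much less.

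**The case against.** The strongest reply is that trigger and criterion are not the same. The trigger sets no minimum number of signs, whereas the LOS standard asks for two and the CoNS rule asks for overt ones. That stands, and it is why the rule rejects some contaminants. A reader might infer that nearly every CoNS contaminant becomes a case; the documents do not support this. The five-day antibiotic clause might be a further filter if it governs the whole list. The grammar leaves that open, and continued treatment may itself respond to the positive culture.

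Three other strong readings also fail:

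- *CRP plays no part.* It is named as a diagnostic marker and physicians may weigh it. What is absent is a fixed CRP condition in the CoNS rule.
- *No repeat culture can exist because one bottle is drawn.* The text gives a volume, not a number of bottles, and provides for another culture at therapy changes. That culture is, however, not a confirmation rule for CoNS.
- *The general sign rule is equally flawed for every organism.* Counting a recognised pathogen in a symptomatic infant is simply the endpoint; contamination is a question specific to CoNS here.

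On size, 42 per group is the stated minimum. The plan expects 54–101 complete cases and more controls than cases: 54 cases with two controls each (an illustrative ratio) would have 92–74% power at 10–30% contamination. Contaminated cases are symptomatic infants, so a control-like 30% dysbiosis rate is pessimistic.

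Finally, a sensitivity analysis may be in an analysis plan that is not at hand. Its absence is therefore not the complaint. The complaint is that the classification rule stated here discriminates poorly. Physician judgement and training in aseptic sampling help, but fix no reproducible criterion.

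**Conclusion.** The point holds in a limited form. After 72 hours the CoNS criterion overlaps heavily with the culture trigger, and no fixed independent criterion supplements it, so some contaminants may be counted as proven LOS. How many cannot be read from the article.

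Under the worst-case assumption of Step 3, power is at risk mainly at the low end of recruitment and is largely preserved at 101 cases. A reader might take the drop to 50% as the expected result. It is not: it combines the highest assumed contamination, control-like microbiomes and the bare minimum sample. The effect on incidence and on the CoNS share of the AMR profile needs attention at any sample size. This is a worthwhile and inexpensive improvement, and does not invalidate the design.

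**What to change.** For endpoint classification and analysis only, flag every CoNS-only episode and prespecify that the incidence, Cox and microbiome results are repeated in two ways:

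- **(a)** without CoNS-only episodes as proven LOS;
- **(b)** counting a CoNS-only episode as proven LOS only if the recorded CRP within 48 hours exceeds the protocol's 10 mg/l. Episodes with missing CRP are handled as in (a).

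In each analysis, class the remaining symptomatic CoNS-only episodes as clinical sepsis, so that they are neither primary cases nor controls. Because the definitions section ties clinical sepsis to the absence of a blood culture, the wording must state that it covers symptomatic infants whose CoNS isolate was not accepted.

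The cost is a few sentences and repeated runs of planned models. Isolates and CRP are already recorded, and no care changes. The downside is fewer events in these analyses, with some true CoNS sepsis moved to clinical sepsis. For that reason (a) and (b) are offered as checks on whether conclusions depend on the rule, and not as a replacement primary definition.
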